### Interventions

2.7

All participants will receive basic treatment prior to intervention. Per the *Chinese Guidelines for Secondary Prevention of Ischemic Stroke and Transient Ischemic Attack* (21), this basic treatment includes three aspects: (1) Controlling risk factors such as blood pressure and blood glucose; (2) Administering regular-dose aspirin for antiplatelet aggregation (if no contraindications) and atorvastatin for lipid regulation and plaque stabilization; (3) Providing health education on diet, lifestyle, and physical activity. Participants in the acupuncture and sham acupuncture groups will receive a 3-week intervention: one 30-min session daily, 5 times weekly (2 rest days on weekends). The active drug group will take betahistine mesilate tablets orally three times daily for three consecutive weeks.

In the acupuncture group (Group A), participants will undergo acupuncture with filiform needles (Huatuo brand, Suzhou, China; Figure 2) at the following acupoints: Baihui (GV20), bilateral Fengchi (GB20), bilateral Wangu (GB12), and bilateral Taichong (LR3) (Figure 3; Table 2). After needling the acupoints, needles will be twisted 90–180° and lifted and inserted by 3–5 mm to induce a *deqi* sensation. This stimulation will be applied immediately after insertion and then repeated at 10-min intervals during the 30-min needle retention period, yielding three stimulation episodes per treatment session.

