**Figure 3 fig3:**
[figure not shown]
Location of acupoints and non-acupoints.

**Table 2 tab2:** Location of acupoints and non-acupoints.

Acupoints and non-acupoints	Location
GV20 (Baihui)	On the head vertex, at the midpoint of the line connecting the two ear apices, 5 cun above the anterior hairline midpoint.
GB20 (Fengchi)	In the anterior region of the neck, inferior to the occipital bone, in the depression between the origins of sternocleidomastoid and the trapezius muscles.
GB12 (Wangu)	On the lateral head (posterior to the ear), in the depression inferior to the mastoid process at the sternocleidomastoid attachment.
LR3 (Taichong)	On the foot dorsum, 1 cun proximal to the 1st-2nd metatarsophalangeal joint, between the 1st and 2nd metatarsal bones.
Non-acupoint 1	1.5 cun lateral to GV20 (Baihui)
Non-acupoint 2	1 cun inferior to GB9 (Tianyou, on the lateral neck, posterior to the sternocleidomastoid muscle, at thyroid cartilage upper border level).
Non-acupoint 3	1.5 cun lateral to GB21 (Jianjing, on upper back, midpoint of C7 spinous process-acromion line, approximately 4 cun lateral to posterior midline).
Non-acupoint 4	1 cun superior to LR3 (Taichong).

In the sham acupuncture group (Group B), participants will receive treatment with retractable blunt needles (Streitberger type, Suzhou, China; Figure 2) at non-acupoints (Figure 3; Table 2), using skin-non-penetrating stimulation.

In the active drug group (Group C), participants will receive betahistine mesilate tablets (trade name: Minshilang).

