#### Clinical data analysis

2.10.1

Clinical outcomes will be analyzed using SPSS 23.0 statistical software, with a significance level of *p*-value < 0.05. All analyses will be performed by independent statisticians blinded to group assignments and interventions. Two core analysis sets will be used: (1) Full Analysis Set (FAS): All randomly assigned participants who received at least one treatment session. Missing values for primary outcomes will be imputed using the Last Observation Carried Forward (LOCF) method, and FAS results will be the primary analytical basis. (2) Per Protocol Set (PPS): Participants with no exclusion criterion violations, ≥10 completed acupuncture sessions, and at least the Week 3 assessment. PPS results will serve as supplementary references. Relevant statistical analyses will also cover case distribution analysis, which will calculate the sample size of each analysis set per group, case distribution across study centers, and total numbers of dropouts and withdrawals (with respective reasons), and present these data in detailed tables.

The correlation between baseline treatment expectation and changes in DHI will be examined using Pearson correlation. In addition, multiple linear regression models will be constructed with change in DHI as the dependent variable, and baseline expectation score, treatment group, baseline DHI, age, and sex as independent variables, to examine whether expectation independently predicts treatment response. Exploratory interaction terms between treatment group and expectation will be tested to evaluate whether the magnitude of the acupuncture effect differs according to baseline expectation level.

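### The per-protocol set requires at least 10 acupuncture sessions from everyone, a rule that no participant in the tablet arm can meet

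*Protocol article*

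**What the plan says.** Section 2.10.1 (Clinical data analysis) of the protocol article defines two analysis sets. The FAS is "All randomly assigned participants who received at least one treatment session", and "FAS results will be the primary analytical basis". The PPS is "Participants with no exclusion criterion violations, ≥10 completed acupuncture sessions, and at least the Week 3 assessment", and "PPS results will serve as supplementary references". Neither definition has a clause specific to an arm. The same section announces a case-distribution analysis, "which will calculate the sample size of each analysis set per group".

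Section 2.7 (Interventions) describes the treatments. For the needling arms: "Participants in the acupuncture and sham acupuncture groups will receive a 3-week intervention: one 30-min session daily, 5 times weekly". For the third arm: "The active drug group will take betahistine mesilate tablets orally three times daily for three consecutive weeks". The description of Group C at the end of that section again mentions tablets only: "In the active drug group (Group C), participants will receive betahistine mesilate tablets".

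**The concern.** The PPS adherence test counts something that exists in only two of the three arms. The drug arm therefore either fails it completely or has to be let in by a rule that is not written down.

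Section 2.1 (Objectives) makes the comparison of real acupuncture, sham acupuncture and active drug a primary objective. The per-protocol analysis is the plan's stated supplement to the FAS result for that comparison. If the rule is followed, the supplement is unavailable for acupuncture versus drug. If it is waived, the supplement compares participants selected for adherence with participants who are not, and a difference between the arms could reflect that selection. If a tablet threshold is chosen later, it is not pre-specified. A late choice also sits badly with the statement in section 2.10.1 that the statisticians are blinded to group, because an unwritten exception for Group C can be applied only by someone who knows who is in Group C.

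**Working it through.** This is a check of one definition against the arm descriptions. Arithmetic serves only to size it.

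**Inputs.** Section 2.5: assumed mean DHI 21 (acupuncture), 33 (sham) and 30 (drug), SD 20, power 0.90, alpha 0.05, 66 per group, 15% attrition, 78 per group and 234 in total. Section 2.7: needling 5 times weekly for 3 weeks in Groups A and B; tablets only in Group C. Section 2.10.1: the PPS threshold of 10 sessions.

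**Step 1, the plan's own numbers.** Grand mean = (21 + 33 + 30)/3 = 28. Sum of squared deviations = 49 + 25 + 4 = 78. For a one-way ANOVA F-test the noncentrality is n × 78/20² = n × 78/400. Power is 0.8957 at n = 65 and 0.9005 at n = 66, so 66 per group is reproduced. Attrition: 66/(1 − 0.15) = 77.6, rounded up to 78; 3 × 78 = 234. Both figures match. The PPS rule plays no part in this calculation.

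**Step 2, the threshold in the needling arms.** Planned sessions = 5 × 3 = 15. The threshold is 10/15 = 66.7% of planned sessions.

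**Step 3, the rule read literally.**

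| Group | Treatment | Sessions possible | Largest possible PPS |
|---|---|---|---|
| A | Acupuncture | 15 | 78 |
| B | Sham (sham sessions counted) | 15 | 78 |
| C | Betahistine tablets | 0 | 0 |

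The upper limit is 78 + 78 + 0 = 156 of 234. The number of drug participants is zero whatever their adherence, so there is no per-protocol estimate for acupuncture versus drug or for sham versus drug. Acupuncture versus sham remains computable.

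**Step 4, the rule waived for Group C.** Groups A and B are limited to participants with at least 10 of 15 sessions. In Group C anyone with a Week 3 assessment and no exclusion-criterion violation qualifies, whatever the intake. The documents give no adherence rates, so the resulting distortion cannot be quantified.

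**Step 5, consistency within section 2.10.1.** The section promises the size of each analysis set in each group. A drug-arm PPS was therefore evidently intended, and the stated rule cannot deliver one.

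**Step 6, the FAS wording.** Section 2.7 uses the term for a session of treatment only in connection with needling. Its counterpart for tablets is not stated, but one dose is the natural reading, and on that reading the FAS includes Group C.

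**The case against.** **Severity.** The strongest counter-argument is that the PPS is supplementary. The FAS carries the primary analysis, the sample size does not depend on the PPS, and acupuncture versus sham is still available per protocol. All of this stands and limits the weight of the point.

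**Selective literalism.** An empty drug arm follows from reading the rule strictly for Group C while counting non-penetrating sham sessions as acupuncture sessions for Group B. A fully strict reading would exclude sham as well; a charitable one takes the threshold to apply to the needling arms only. The charitable reading is probably what was meant, but it leads to the one-sided filter in Step 4. The ambiguity about sham is a further reason to write the rule by arm.

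**The unseen documents.** A full protocol or SAP may contain a drug-arm criterion, and its absence from a condensed article would not by itself be a finding. Here, however, the article states a rule for all participants, and that rule gives the wrong result for one arm. The printed sentence needs correcting in either case.

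**A stronger reading of the FAS.** A reader might infer that the drug arm also fails the FAS, or that dropping non-starters biases the primary comparison with drug. The documents support neither. Randomised and treated at least once is a conventional definition and extends naturally to one dose. Participants in Group C know that they take tablets, and the masking steps in section 2.6 cover only the acupuncture and sham groups, so differential non-starting is possible. But no non-start rate is given and nothing shows that such bias occurs.

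**Conclusion.** The point holds for the PPS. As written, 0 of 78 drug participants can qualify, the PPS is capped at 156 of 234, and the supplementary per-protocol comparison with drug cannot be made. Waiving the rule for Group C replaces an empty arm with a 67% session filter on two arms and no adherence filter on the third. The count of zero rests only on Group C having no acupuncture sessions, which section 2.7 makes clear; the cap of 156 also assumes that sham sessions count.

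The size is modest. The defect is certain but confined to a supplementary analysis, and it changes neither the sample size nor the primary FAS result. The FAS issue is one of loose wording, not demonstrated bias.

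**What to change.** 1. **PPS.** State adherence by arm: at least 10 of 15 sessions, real or sham, in Groups A and B, and a pre-specified, comparable criterion based on recorded tablet intake in Group C. Keep all other PPS criteria identical across arms. The sponsor should set the tablet threshold before unblinding. Carrying over 67% is one option, but nothing in the documents equates that fraction of tablets with 10 of 15 sessions.
2. **Fallback.** If intake was not recorded for participants already treated, restrict the per-protocol analysis to acupuncture versus sham and say so.
3. **FAS.** Replace the session wording with a condition that covers all arms, such as at least one session or one dose.
4. **Optional.** An analysis of all randomised participants would avoid any differential exclusion of non-starters in the unmasked drug arm. If it is added, its handling of missing data needs thought: under the LOCF rule in section 2.10.1, a never-treated participant with no later data would simply carry the baseline value forward.

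**Cost.** Items 1 and 3 need a sentence or two each in the analysis-set definitions, and no change to the sample size. The practical cost is recording tablet intake in Group C. The article does not mention tablet counts. Recruitment was scheduled to start on July 1, 2025 (section 2.3.1) and the article appeared in March 2026, so if enrolment began on schedule, intake for participants already treated may not be recoverable. It is worth checking this now.

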#### fMRI data analysis

2.10.2

##### T1-weighted data

2.10.2.1

Whole-brain gray matter volume (GMV) will be calculated from 3D T1-weighted images using voxel-based morphometry (VBM) in FSL 5.0.9.1 software. Workflow: ① Remove non-brain tissues using the Brain Extraction Tool (BET). ②Segment brain tissues into gray matter, white matter, and cerebrospinal fluid using the FMRIB Automated Segmentation Tool (FAST). ③Nonlinearly register individual gray matter images to the ICBM-152 standard gray matter template using the FNIRT tool, then construct a preliminary study-specific template via averaging and x-axis flipping. ④Re-register individual gray matter images to the preliminary template, then average to generate a final symmetric study-specific template. ⑤Modulate registered gray matter images using the Jacobian matrix of the deformation field to produce GMV maps. ⑥ Smooth GMV images with a 3 mm Gaussian kernel (full width at half maximum, FWHM ≈ 7 mm).

##### rs-fMRI data

2.10.2.2

① *Functional Connectivity (FC)*: Defined as the temporal correlation of neurophysiological indices across brain regions, depicting the relationship between neuronal activity patterns of anatomically separated regions and reflecting functional communication levels.

② *Amplitude of Low-Frequency Fluctuations (ALFF)*: Quantifies the intensity of spontaneous low-frequency neural oscillations, directly reflecting local brain functional status.

③ *Regional Homogeneity (ReHo)*: Reflects local brain function by quantifying the synchrony of blood-oxygen-level-dependent (BOLD) time series between a voxel and its neighbors using Kendall’s coefficient of concordance. Synchrony variations are closely associated with neural activity and brain function changes (22).

④ *BOLD*: fMRI uses BOLD signals to dynamically represent brain activity. In the resting state, spontaneous BOLD fluctuations show spatial synchrony across functionally relevant brain regions—enabling identification of multiple resting-state functional connectivity networks. Abnormalities and recovery of functional connectivity in networks such as the default mode network (DMN) and executive control network (ECN) are directly linked to post-stroke recovery. These abnormalities correlate with post-stroke white matter structural damage, illuminating the relationship between structural injury and functional deficits. We aim to investigate DMN-related functional connectivity by examining BOLD signal changes across brain regions (23).

##### DTI data

2.10.2.3

① *Fractional Anisotropy (FA)*: A quantitative index of anisotropic diffusion in DTI, enabling detection of subtle changes in white matter diffusion properties. FA values reflect axonal integrity, with abnormalities indicating axonal damage. Baseline whole-brain mean FA is associated with subsequent vertigo severity changes (24). We will extract pre- and post-treatment mean FA values of the whole-brain white matter skeleton for each patient and correlate them with DHI score changes to explore whether acupuncture ameliorates vertigo by modulating white matter integrity.

② *Mean Diffusivity (MD)*: Quantifies overall water molecule diffusion freedom, indirectly reflecting physiological structural integrity and pathophysiological changes in the nervous system. Elevated MD indicates impaired fiber tract integrity, leading to delayed/disrupted neural signal transmission and functional connectivity abnormalities (25).

Furthermore, the Pearson correlation analysis between the clinical results and fMRI results will be conducted to investigate the potential correlation between symptom improvements and brain activity changes elicited by different interventions.

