### Objectives

2.1

This study has two primary objectives: (1) compare the clinical efficacy of real acupuncture, sham acupuncture, and active drugs for PSVV to verify acupuncture’s efficacy and safety for this condition; (2) explore the central nervous system mechanisms of acupuncture for PSVV using multimodal MRI.

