### Design and setting

2.2

This is a multicenter, double-blind, randomized, controlled study that meets the recommendations of the Standard Protocol Project: Intervention Trials guidelines (19). This trial will be conducted in four clinical subcenters: the Affiliated Hospital of Chengdu University of Traditional Chinese Medicine, Chongqing Hospital of Traditional Chinese Medicine, Shuangliu District Hospital of Traditional Chinese Medicine in Chengdu, and Longquanyi District Hospital of Traditional Chinese Medicine in Chengdu. A total of 234 eligible participants will be randomly assigned to the active drug group, the acupuncture group, and the sham acupuncture group (1:1:1 allocation ratio). Participants will be evaluated at baseline, week 3, week 11, and week 23. Transcranial Doppler ultrasonography (TCD) and multimodal MRI will be performed at baseline and at week 3. All outcome assessors will be blinded to group assignment. The flowchart and results evaluation schedule of this trial are shown in Figure 1 and Table 1. The protocol was approved by the Medical Ethics Committee of the Affiliated Hospital of Chengdu University of Traditional Chinese Medicine (approval no. 2025KL-062) (Supplementary File 1) and is registered with the International Traditional Medicine Clinical Trial Registration Platform (registration no. ITMCTR2025001283).

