#### Inclusion criteria

2.3.2

According to the Bárány Society (2), vascular vertigo can result from either central lesions (brainstem, cerebellar, or supratentorial) or isolated labyrinthine infarction/hemorrhage. In the present study, only patients with central vascular vertigo following ischemic or hemorrhagic stroke are eligible.

Inclusion requires: (1) neuroimaging evidence of a lesion involving the vertebrobasilar territory or supratentorial central vestibular structures (e.g., brainstem, cerebellum, thalamus, insula, temporo-parietal cortex) that is judged by the investigator to be responsible for the vertigo; (2) aged 30–80 years (inclusive), regardless of gender; (3) ≥ 2 weeks since the onset of cerebral infarction or cerebral hemorrhage, with persistent vertigo or postural instability for ≥1 week (vertigo-related symptoms must not precede the diagnosis of cerebral infarction/hemorrhage); (4) Barthel Index (BI) score >40; (5) stable vital signs and overall clinical condition; ability to complete a vertigo diary as instructed; (6) not participating in any other trials during the study period and signing a written informed consent form.

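### The white-matter mechanism question is tied to an FA–DHI correlation with no stated treatment-group term, which stroke recovery alone can produce

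*Protocol article*

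**What the plan says.** Section 2.1 (Objectives) gives as the second of two primary objectives to "explore the central nervous system mechanisms of acupuncture for PSVV using multimodal MRI". Section 2.2 (Design and setting) says that "multimodal MRI will be performed at baseline and at week 3", and Table 1 does not restrict the scans by arm.

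The imaging inference is in section 2.10.2.3 (DTI data). Mean FA over the white matter skeleton is to be taken before and after treatment in each patient, and the analysts will "correlate them with DHI score changes to explore whether acupuncture ameliorates vertigo by modulating white matter integrity". The section closes by adding that "the Pearson correlation analysis between the clinical results and fMRI results will be conducted", to look at the "potential correlation between symptom improvements and brain activity changes elicited by different interventions". Sections 2.10.2.1 and 2.10.2.2 describe preprocessing and define indices; they state no comparison of arms.

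Three other statements bear on how such correlations can be read:
- Section 2.3.2 admits patients from "2 weeks since the onset of cerebral infarction or cerebral hemorrhage" and states no upper limit.
- Section 2.10.2.2 says that abnormality and recovery of network connectivity "are directly linked to post-stroke recovery".
- Section 2.10.2.3 itself says: "Baseline whole-brain mean FA is associated with subsequent vertigo severity changes". That sentence does not mention treatment.

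**The concern.** Whether acupuncture acts through white matter is a causal question about a treatment. The statistic assigned to it relates two patient-level quantities to each other and contains no treatment variable. Anything that moves both quantities will produce the correlation, and recovery after stroke is an obvious candidate. The article supplies that rival explanation itself, by linking connectivity to recovery and baseline FA to later vertigo change.

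Splitting the correlation by arm does not remove the problem. Within the acupuncture arm, patients further along in recovery may show both more FA change and more DHI change, whatever the needles did. The correlation can also miss a true effect: if acupuncture raised FA by the same amount in every treated patient, the within-arm correlation would not change.

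At stake is the reading of the second primary objective. A significant correlation could be presented as support for a white-matter mechanism when FA had changed equally in all arms.

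**Working it through.** **Sample size.** The article gives no figure for the MRI analyses, so the DHI sample size serves as a reference. Section 2.5 assumes means of 21, 33 and 30, SD 20, α 0.05 and power 0.90. The grand mean is 28 and the squared deviations sum to 49 + 25 + 4 = 78. With 66 per arm the noncentrality is 66 × 78 / 20² = 12.87. The three-group F test on 2 and 195 degrees of freedom then has power 0.9005, so 66 per arm and 198 in total reproduce. Allowing for attrition, 66 / 0.85 = 77.6, rounded up to 78 per arm and 234 in total. The sample size is not at issue. How many of these patients will be scanned is not stated.

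**Illustration by formula (assumed correlations).** Suppose FA change and DHI change each correlate r with a recovery factor, such as time since stroke, and are otherwise unrelated. They then correlate ρ = r². With r = 0.4, ρ = 0.16; with r = 0.5, ρ = 0.25. The chance of a two-sided p < 0.05 is approximately Φ(atanh(ρ) × √(n − 3) − 1.96).

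| ρ | n = 198, pooled | n = 66, one arm |
|---|---|---|
| 0.16 | Φ(0.1614 × 13.96 − 1.96) = Φ(0.29) ≈ 62% | Φ(0.1614 × 7.94 − 1.96) = Φ(−0.68) ≈ 25% |
| 0.25 | Φ(0.2554 × 13.96 − 1.96) = Φ(1.61) ≈ 95% | Φ(0.2554 × 7.94 − 1.96) = Φ(0.07) ≈ 53% |

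Acupuncture has no effect on FA in any cell. The two columns are alternative analyses, because the article does not say whether the correlation is pooled or by arm.

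**Simulation.** There were 4,000 trials per setting, with 66 per arm and no acupuncture effect on FA. A shared recovery factor induced the stated correlation. DHI benefits over sham were set at 12/20 = 0.6 SD for acupuncture and 3/20 = 0.15 SD for drug, from the means in section 2.5. Share of trials with p < 0.05:

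| Recovery-induced correlation | Pooled correlation | Correlation in acupuncture arm | Acupuncture versus sham, FA change |
|---|---|---|---|
| 0.2 | 78% | 37% | 5.0% |
| 0.3 | 99% | 69% | 5.2% |
| 0.4 | 100% | 92% | 4.7% |
| 0.5 | 100% | 99% | 5.2% |

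The contrast simulated was an unadjusted t test of FA change. It stays near its nominal 5% at every setting, because randomisation balances recovery between the arms.

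**What the contrast could detect.** If every patient were scanned, the detectable standardised difference in FA change is (1.960 + 1.282) × √(2/n) at 90% power: 0.56 SD with 66 per arm and 0.52 SD with 78. At 80% power the figures are 0.49 and 0.45 SD. Fewer scans would raise them.

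**The case against.** The strongest reply is that this is condensation, not choice. The clinical analysis section names no between-group test for DHI or any other outcome, so the lack of one for MRI says little about intent. A statistical analysis plan that is not shown may contain it. Multimodal MRI is a secondary outcome scheduled without restriction by arm, the closing correlation is worded as an addition and refers to different interventions, and the Discussion justifies the sham device as the way to isolate acupuncture's specific effects. The aim is worded as exploration throughout, and the Discussion already concedes confounding of resting-state fMRI by vascular disease, ageing and medication.

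Much of this stands. A reader might infer that the sham arm will not be used as a comparator for MRI, that the design cannot attribute brain change to acupuncture, or that the trial will conclude that acupuncture works through white matter. The documents support none of these. They are silent on the comparator, they plan a randomised sham arm scanned at both visits, and they commit to no causal conclusion from a significant correlation. The percentages above also rest on assumed correlations. The figure of 198 is probably generous, since all scans are at one of the four centres (section 2.8.2.5) and the Discussion says that right-handed patients will be recruited for MRI.

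One part of the point does not depend on silence. The article names the statistic meant to address the mechanism question, and that statistic cannot separate acupuncture from recovery. A between-arm test elsewhere would leave that sentence unchanged. The reference to different interventions suggests correlations by arm at most, which do not test acupuncture against sham. Section 2.10.1 does put treatment group, and its interaction with expectation, into the expectation model, so the article states group terms in at least one place.

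**Conclusion.** The point holds in a limited form. As stated, the FA–DHI correlation does not distinguish an acupuncture effect on white matter from recovery shared by all arms, and a significant result could be misread as evidence of mechanism. With no acupuncture effect on FA, a recovery-induced correlation of 0.16 would be significant in about 62% of trials if 198 patients were pooled, or about 25% within one arm of 66. These sizes depend on the assumed correlation and on the unknown number scanned. That recovery alone can produce the correlation does not depend on them. Because the aim is exploratory and the randomised data needed for a sound comparison are already planned, this is a cheap improvement to the stated analysis and not a defect of the design.

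**What to change.** In section 2.10.2.3, state that the mechanism question is addressed first by a randomised acupuncture-versus-sham comparison of week-3 skeleton-wide mean FA, by ANCOVA adjusted for baseline FA. Lesion category (already recorded under section 2.4) and time since stroke may be added as covariates.

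Label the FA–DHI correlation and the other imaging–clinical correlations descriptive and hypothesis-generating, not evidence that acupuncture acts through white matter.

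Any follow-up model linking FA change to DHI change should include treatment group and be reported as exploratory. FA change is measured after randomisation, so randomisation does not protect that link. An arm-by-FA-change term tests whether slopes differ between arms; it does not test mediation.

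The cost is a change of wording and modest extra analysis on scans already scheduled. The downside for the authors is that nominally significant correlations would no longer support a mechanism claim.

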To ensure reliable results, participants will be randomly assigned to groups, with outcome assessors and statisticians blinded to group assignments to minimize potential bias. However, this trial has several limitations. Owing to the inability to blind among the acupuncturists, the use of self-reported outcomes, and the potential placebo effect of acupuncture, the study results may be prone to bias. Additionally, a challenge for clinical applications of rs-fMRI is the potentially confounding effect of concomitant vascular diseases, aging, or medication on the neurovascular coupling and consequently the fMRI imaging response (33). Therefore, quality control methods are prerequisites for reliable results: (1) recruit right-handed patients for MRI to avoid dominant hand effects on brain structure and function; (2) acupuncture procedures will be strictly performed by trained, certified practitioners with at least 3 years of experience following standardized protocols; (3) Standardized, highly repeatable acupuncture interventions; (4) participants will be instructed to maintain their usual lifestyle for 24 h before scanning, avoiding late nights, smoking, and consumption of coffee or tea. During scanning, participants will close their eyes and wear earplugs. Following the scan, participants will document sensations experienced during the procedure, including somatic sensations, psychological state, and thought activity, to explore the influence of various factors on test outcomes.

In summary, this trial will evaluate the efficacy of acupuncture for PSVV and explore its central mechanisms. It will provide evidence for acupuncture’s effectiveness in treating PSVV and preliminarily investigate its neuroplasticity effects. Additionally, quality control methods will be implemented to enhance the reliability of results. We anticipate this study will offer guidance for the early treatment of PSVV. Findings will be reported according to the Consolidated Standards of Reporting Trials (STRICTA) guidelines (34).

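### The clinical-imaging link is an unadjusted Pearson correlation, although the article itself names vascular disease, ageing and medication as potential confounders of the fMRI response and none of its listed controls deals with them

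*Protocol article*

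**What the plan says.** Section 2.10.2.3 (DTI data) gives the analysis joining the clinical and imaging results: "the Pearson correlation analysis between the clinical results and fMRI results will be conducted". The variables are symptom improvement and change in brain activity. The same section extracts mean FA before and after treatment and correlates it with DHI change. Neither analysis names a covariate.

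The Discussion lists limitations. The last is the "potentially confounding effect of concomitant vascular diseases, aging, or medication on the neurovascular coupling", and through it on the fMRI response. The next sentence begins "Therefore, quality control methods are prerequisites for reliable results" and gives four items:

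1. Handedness: "recruit right-handed patients for MRI to avoid dominant hand effects on brain structure and function".
2. The training, certification and minimum experience of the acupuncturists.
3. A uniform, reproducible needling procedure.
4. Behaviour before the scan: "participants will be instructed to maintain their usual lifestyle for 24 h before scanning, avoiding late nights, smoking, and consumption of coffee or tea", together with closed eyes, earplugs and a record of sensations after the scan.

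Section 2.10.1 does specify an adjusted model for DHI change, with expectation, treatment group, baseline DHI, age and sex. It contains no imaging variable. Section 2.1 makes the central mechanism one of two primary objectives, worded as exploration.

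**The concern.** Randomization balances the arms. It does not protect a correlation, across patients, between two changes that both occur after randomization. If older patients, or those with more vascular disease, recover differently on the DHI and also show a different change in BOLD measures, the two changes will correlate without any neural mechanism joining them. If the arms are pooled, treatment group can do the same: an intervention that moves both variables produces a correlation even when one change does not cause the other.

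The sample leaves room for this. Every patient has had a stroke and ages run from 30 to 80 (section 2.3.2). Only severe cardiovascular disease is excluded (2.3.3), and aspirin depends on contraindications (2.7). At stake is how the mechanism results are read. The Discussion means to offer them as further evidence on how acupuncture works, and that reading leans on these correlations.

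**Working it through.** **Controls against named confounders.**

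| Control in the Discussion | Vascular disease | Age | Medication |
|---|---|---|---|
| Handedness | no | no | no |
| Acupuncturist training | no | no | no |
| Standardized acupuncture | no | no | no |
| Behaviour for 24 h before the scan, scan conditions | no (short-term exposures only) | no | no |

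**The plan's own figure.** The article gives no number for the imaging correlation, so the only sample size available is the one for the DHI (section 2.5). Inputs: means 21, 33 and 30, SD 20, α 0.05, power 0.90. The grand mean is 28 and the squared deviations sum to 49 + 25 + 4 = 78. For a one-way ANOVA F test the noncentrality is λ = n × 78/400. At n = 65, λ = 12.68 and power is 0.896. At n = 66, λ = 12.87 and power is 0.900. So 66 per group (198 in all) reproduces, and 66/0.85 = 77.6 rounds up to 78 per group, 234 in all. I use 66 and 198 below as stand-ins for one arm and for all arms pooled. They are not stated scan numbers.

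**Size of the effect.** Assumptions: no true link, and one confounder with correlation c to each of DHI change and imaging change. The induced correlation is r = c × c. By Fisher's z, the mean of the test statistic is m = atanh(r) × √(n − 3), and the two-sided rejection rate is P(Z > 1.96 − m) + P(Z < −1.96 − m). Here √63 = 7.94 and √195 = 13.96.

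| c | r | m, n = 66 | rate, n = 66 | m, n = 198 | rate, n = 198 |
|---|---|---|---|---|---|
| 0.2 | 0.04 | 0.32 | 6.2% | 0.56 | 8.6% |
| 0.3 | 0.09 | 0.72 | 11.1% | 1.26 | 24.3% |
| 0.4 | 0.16 | 1.28 | 24.9% | 2.25 | 61.6% |

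A simulation with 10,000 runs per cell agrees: 6.3%, 11.0% and 25.1% at n = 66, and 8.4%, 24.3% and 60.8% at n = 198. In the same runs the partial correlation given the confounder rejected in 4.7% to 5.3%.

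**One anchor for c.** The documents allow only treatment group to be gauged, and only on the DHI side. With the section 2.5 means, the between-arm variance is 78/3 = 26. Taking 20 as the within-arm SD, the share of variance due to arm is 26/(26 + 400) = 0.061, a correlation of √0.061 = 0.25. The imaging side is unknown.

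**The case against.** The strongest case against has five parts.

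- **The controls answer several limitations.** The sentence introducing them follows unblinded acupuncturists, self-report and placebo effects as well as the fMRI point. Items 2 and 3 plainly serve the acupuncture side. This stands. A reader might infer that the article claims the four items remove neurovascular confounding. It does not; it discloses the limitation. What remains is that nothing in the list, and nothing in the stated analysis, acts on it.
- **Change scores help.** Age and chronic vascular disease hardly alter in three weeks, so their effect on signal level largely cancels and only an effect on the change remains. This stands and lowers the likely size. Less cancels for FA, which is described through its pre- and post-treatment values. On the other hand, the Discussion's warning concerns rs-fMRI and is not extended to FA.
- **There is partial handling elsewhere.** Severe cardiovascular disease is excluded, background treatment is common to all arms, lesion location is documented (2.4), and history and medication are recorded (Table 1). True, but none of these data is carried into the stated correlation.
- **n = 198 is not a scan number.** All fMRI is done on one hospital's scanner (2.8.2.5) in a four-centre trial, and the Discussion limits MRI to right-handed patients. The number scanned may be smaller, and analysis by arm is a natural reading. This stands, so the n = 66 column must be read beside the other.
- **The analysis is exploratory and could be refined in an unseen analysis plan.** It is exploratory, and that limits the weight of the point. But the article commits to Pearson here while spelling out covariates for another analysis of DHI change.

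A reader might also infer that imaging changes in the betahistine arm are haemodynamic. The documents attribute no such action to the drug. Within that arm, assignment is constant and cannot confound the correlation.

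**Conclusion.** The point holds as an inexpensive improvement to an exploratory analysis. The article names three potential confounders of the fMRI response, lists no control that deals with them, and states the clinical-imaging link as a bivariate correlation. A mechanism finding could therefore partly reflect age, vascular status or medication, or treatment group under pooling.

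The size cannot be fixed from the documents. For c of 0.2 to 0.4, the false-positive rate per measure is about 6% to 25% at n = 66 and 8.6% to 62% at n = 198, against 5%. The c values, the sample sizes and the absence of a true link are all assumptions. A reader might take 62% as the expected error rate. It is the top of the range: it needs a correlation of 0.4 with both changes, and 198 scanned patients analysed together. Nor does any of this bear on the randomized DHI comparison.

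**What to change.** In section 2.10.2.3, make the main clinical-imaging analysis a regression of DHI change on imaging change, or the equivalent partial correlation. Adjust for age, sex, baseline DHI, and baseline vascular history and concomitant medication, and for treatment group if the arms are pooled. State whether the arms are pooled. Treat the FA analysis in the same way, and say whether FA enters as a level or as a change. Report simple Pearson coefficients as descriptive.

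Keep TCD change out of the main model. It is measured after randomization and may lie on the path from treatment to symptom relief, so conditioning on it could remove a real effect or add bias. Use it at most in a sensitivity analysis.

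Describe the results as hypothesis-generating. In the Discussion, say that the listed controls do not address vascular disease, age or medication, and point to the adjusted analysis.

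The cost is wording and a few degrees of freedom. Age and sex are already used in the section 2.10.1 model, baseline DHI is scheduled, and history, concomitant disease and medication are recorded at enrolment (Table 1). No new data are needed.
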